### Data collection

#### Level I to III

##### Strategy

Rapid assessment individual interviews and focus groups will collect qualitative information on policy makers' considerations and need for information for planning the introduction of a cholera vaccination programme. This phase of the study will also involve data collection with health care providers and community leaders on their perceptions of cholera, its importance to community residents, and their interest in the OCV. This research will explore policy issues and processes, as well as barriers and enabling factors that are likely influences in the introduction of a vaccine against cholera. The descriptive data of the rapid assessment interviews and focus groups can be related to and compared with level IV data. The approximate duration of this phase of the study is four weeks. It will be conducted following the mass OCV campaign in order to ground perspectives on the acceptance of an OCV in real world contexts and experiences.

##### Instrument

In-depth interviews and group discussions are open-ended and semi-structured to both cover critical topics and allow the respondents to identify and discuss what is important to them regarding cholera and the use of a cholera vaccine. For each stakeholder level specific interview and discussion guidelines have been created, translated and orally back-translated to ensure their intelligibility and appropriateness. Two experienced field researchers will conduct the research either in English or Kiswahili depending on the respondents. Each session will last approximately one hour.

##### Sampling

The following groups will be selected purposively:

- Policy makers (n = 10–20) including national and regional policy makers (e.g. from MoHSW, international non-governmental organisations);

- Allopathic and traditional health care providers (n = 6–8 per island) working in the target areas and district hospitals;

- Formal and informal local government and community leaders and teachers (n = 6–8 per island) from the target areas (e.g. Shehas, secular and Islamic teachers).

#### Level IV: preparatory phase

##### Strategy

Community residents will be approached on both islands and information collected in focus group discussions. Data will be collected to complete or expand the lists of variables of the different EMIC interview sections mentioned above. The approximate duration of this phase is two weeks with one team working per site. This phase must be completed before phase 1 starts.

##### Instrument

A FGD guideline was drafted which covers all the relevant issues of the EMIC interviews. Each team will consist of a moderator and a note taker.

##### Sampling

- Sample: adults (≥ 18 years) from both communities;

- Sampling frame: registers from Shehias adjacent to the target Shehias;

- Sampling method: stratified purposive sample, by gender and age group (18–45 years, >45 years);

- Exclusion criteria: belonging to other stakeholder level I to III;

- Sample size: n = 48–64, eight FGD with each having ca. 6–8 respondents (4 FGD per site)

#### Level IV: phase 1 (pre-vaccination)

##### Strategy

Community residents will be approached on both islands and information collected through EMIC interviews. Data will be collected i) to clarify the local features of cholera and shigellosis; and ii) to identify social and cultural determinants of anticipated OCV acceptance. The approximate duration of this phase is about ten weeks. Three teams each per site will be working simultaneously. This phase must be completed before the social mobilisation and vaccination campaign starts.

##### Instrument

An EMIC interview for phase 1 was drafted and, once it has incorporated information from the preparatory phase (FGD), will be pilot tested and finalised before implementation. Since the general adult population – and not cases – will be interviewed, it was decided to introduce the topic to the interviewees by using slightly varying gender-specific vignettes which describe cardinal physical symptoms of cholera and shigellosis. This approach ensures that the interviewees will respond with regard to the clinically relevant conditions and not with regard to local notions of diarrhoeal illnesses labelled by the respective local terms for cholera and shigellosis.

A ten-day workshop will be conducted to train the fieldworkers in interview and data entry skills, to familiarise them with the instrument and to pilot it under field conditions. Each team will consist of an interviewer and a note taker. Narrative data will be translated and typed on a daily basis by the teams.

##### Sampling

- Sample: adults (≥ 18 years) from both target areas;

- Sampling frame: census and Geographic Information System databases;

- Sampling method: stratified random sample with gender ratio 1:1;

- Exclusion criteria: belonging to stakeholder level I to III;

- Sample size: n = 164 per site, n = 328 per phase

#### Level IV: phase 2 (post-vaccination)

##### Strategy

Community residents will be approached on both islands and information collected through EMIC interviews. Data will be collected i) to clarify the local features of cholera and shigellosis after vaccination, ii) to compare these features with pre-vaccination data, iii) to identify social and cultural determinants of actual OCV acceptance, and iv) to identify barriers to vaccination. The approximate duration of this phase is about ten weeks. Three teams each per site will be working simultaneously. This phase will be implemented after the end of the vaccination campaign.

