##### Sample size calculation for EMIC interviews

The following calculations are based on a 95% significance level and 80% power. The prominence means of the different categories of cultural epidemiological variables will be compared in bivariate analyses (by site, gender, anticipated vs. actual vaccination status) and tested for significant differences using the Wilcoxon rank-sum test. To detect a difference of 0.5 between prominence means with equal standard deviations of 1.5, a sample size of 164 for each group is required. The calculation is based on a two-sample t-test assuming a worst-case scenario, i.e. no underlying distribution in the data, which requires that the sample size derived from the t-test (n = 142) be divided by 0.864 which equals 164.4 [44]. Hence, the overall sample size (two groups per phase times two phases) will be 656, with a sample size of 328 per phase.

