##### Sampling

- Sample: adults (≥ 18 years) from the target areas;

- Sampling frame: vaccination campaign data (vaccinated people), census database after exclusion of vaccinated people (unvaccinated people);

- Sampling method: equally stratified random sample among confirmed vaccinated (two doses of OCV) and unvaccinated (one to two doses) people with gender ratio 1:1;

- Exclusion criteria: belonging to stakeholder level I to III, already interviewed in phase 1, member of household already interviewed;

- Sample size: n = 164 per site, n = 328 per phase

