#### Level IV: quantitative data

Information will be double-entered and cleaned in Epi Info 3.4.3 software. Descriptive statistics and bi- and multivariate analyses will be computed with the statistical analysis programme Stata 10.

Regarding the cholera vignette, the variables related to illness experience (PD), meaning (PC) and help-seeking behaviour (HS) will be coded with a value of two after a spontaneous response, a value of one after a probed response and a value of zero for no response at all to reflect the response style. A value of three will be assigned to the summary variables (i.e. most troubling, most important and most useful). For each category of such a variable, a total prominence will be computed, ranging from zero to five. Thematically similar individual categories will be grouped under specific headings (e.g. "physical symptoms" among PD variables) to enable the analysis of broader concepts of experience, meaning and behaviour. Grouped frequencies will be computed by adding the maximum value based on the response style of each respondent for every single category falling under each group. Calculation of the grouped prominence will follow the same procedure as with the individual variables.

For questions related to the shigellosis vignette, only frequencies of the categories mentioned in relation to illness experience, meaning and help-seeking behaviour will be computed.

Tabulations of the above-mentioned variables will be done after each phase followed by descriptive, bivariate and multivariate analyses to address the research questions.

To test for significant differences (p ≤ 0.05) between two groups, the t-test will be used for normal data and the Wilcoxon rank-sum test for nonparametric data. The Kruskal Wallis test will be used for comparing more than two groups of a nonparametric variable. The Chi^2 ^test and the Fisher's exact test will be applied for comparing two proportions. To compare paired data, i.e. variables between cholera and shigellosis vignettes, the McNemar's Chi^2 ^test, the paired t-test and the paired Wilcoxon test will be used.

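### Phase 2 is sampled 1:1 on vaccination status and phase 1 is not, so unweighted pre/post tests are biased for features that differ by vaccination status unless coverage is 50%

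*Protocol article*

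**What the plan says.** Phase 1 (Level IV: phase 1, Sampling) is a "stratified random sample with gender ratio 1:1", 164 adults per site and 328 in all, drawn from census and GIS databases before the campaign. Its mix of people who will and will not go on to be vaccinated therefore follows the community.

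Phase 2 (Level IV: phase 2, Sampling) is an "equally stratified random sample among confirmed vaccinated" and unvaccinated people, again with gender 1:1, 164 per site and 328 in all. The frames are the campaign data and the census less the vaccinated.

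The second listed objective of phase 2 (Strategy) is "to compare these features with pre-vaccination data". The first is to describe the local features of cholera and shigellosis after vaccination. The third is to find determinants of actual acceptance.

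For two groups, the section Level IV: quantitative data states that "the t-test will be used for normal data and the Wilcoxon rank-sum test for nonparametric data", with Chi-square and Fisher tests for proportions. The protocol mentions no weighting or standardisation to coverage, and states no expected coverage for the target areas.

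**The concern.** The two phases represent different mixtures of the same community. Phase 1 contains eventual acceptors in proportion to coverage; phase 2 contains exactly half. If a feature is associated with accepting the vaccine, the raw phase 2 mean is not the community mean, and the gap from phase 1 includes a part that comes only from the sampling. The third phase 2 objective is to find such features, so the problem falls on the variables of most interest. The pre/post comparison could show a change when nobody's views changed, or hide a real one, in a study meant to inform government policy on the vaccine.

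**Working it through.** **Inputs from the protocol** (Sample size calculation for EMIC interviews)
- The calculation is "based on a 95% significance level and 80% power".
- Effect and spread: "To detect a difference of 0.5 between prominence means with equal standard deviations of 1.5".
- Total sample: it "will be 656, with a sample size of 328 per phase".

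**Inputs assumed, because the protocol does not give them**
- Coverage c: 30% to 90%. The 50% and 30% in the Background are scenarios from a model, not targets for this campaign.
- D, the vaccinated-minus-unvaccinated difference in mean prominence: 0 to 1.0. The value 0.5 is borrowed from the design difference and is not a forecast of D.

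**1. The plan's own figure.** n per group = 2 x (1.96 + 0.842)^2 x 1.5^2 / 0.5^2 = 141.3, rounded up to 142. Then 142 / 0.864 = 164.4, 2 x 164 = 328 and 4 x 164 = 656. This reproduces the "sample size derived from the t-test (n = 142) be divided by 0.864 which equals 164.4" with two-sided 5% testing.

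**2. Bias with no true change.** Let the unvaccinated mean be m.
- Expected phase 1 mean = m + cD.
- Expected pooled phase 2 mean = m + 0.5D.
- Expected difference = (0.5 - c) x D.

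It is zero if c = 0.5 or if D = 0. For D = 0.5 it is +0.10 at c = 30%, and -0.10, -0.15 and -0.20 at 70%, 80% and 90%.

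**3. False-positive rate.** SE of the phase difference = 1.5 x sqrt(2/328) = 0.117. Rate = P(|Z + bias/SE| > 1.96).

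| D | c | bias | rate, simple SE | rate, fuller variance |
|---|---|---|---|---|
| 0.5 | 70% (or 30%) | 0.10 in size | 13.7% | 13% |
| 0.5 | 80% | -0.15 | 24.9% | 24% |
| 0.5 | 90% | -0.20 | 40.0% | 39% |
| 0.25 | 80% | -0.075 | 10% | 10% |
| 1.0 | 80% | -0.30 | 73% | 69% |

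The last column takes 1.5 as the SD within each vaccination group and adds the between-group part: c(1 - c)D^2 to the phase 1 variance and 0.25D^2 to the phase 2 variance that the test uses. The stratified phase 2 mean itself varies only with 1.5^2. For D = 1.0 and c = 80%, the test's SE is sqrt((2.41 + 2.50)/328) = 0.122 and the true SE is sqrt((2.41 + 2.25)/328) = 0.119. The two columns part only when D is large.

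A simulation of the rank-sum test on scores rounded and limited to 0 to 5 (4,000 runs per setting) gave 13%, 23% and 37% for D = 0.5 at 70%, 80% and 90%. It gave about 5% when D = 0 or c = 50%.

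**4. Testing each phase 2 stratum separately against phase 1.** The bias is (1 - c)D for the vaccinated and -cD for the unvaccinated. At c = 80% and D = 0.5 that is +0.10 and -0.40, so splitting does not cure it.

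**5. Contrasts within phase 2.** Against the community contrast, a gender contrast is off by (0.5 - c_f)D_f - (0.5 - c_m)D_m, where f and m denote women and men. This cancels if coverage and D are alike in both sexes; the same holds for site. The vaccinated versus unvaccinated contrast is untouched, as are the logistic slopes for actual acceptance.

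**The case against.** The strongest defence is that no sentence orders all phase 2 respondents to be pooled and tested unweighted against phase 1. The tests are a general list, the sample size counts two groups per phase, and vaccination status is itself a planned comparison. Weighting is a detail that a fuller plan might supply. It stands that weights are not ruled out. But the article fixes the outcome-dependent sample, the pre/post comparison and the tests, and these do not fit together as written. Reporting by stratum does not remove the problem (step 4).

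Three further points stand in full.

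- A reader might infer that every pre/post comparison is biased once coverage departs from 50%. That does not follow: where D = 0 there is no bias at any coverage, and searching for determinants does not presume that every feature is one.
- A reader might infer that all phase 2 gender and site comparisons are biased too. They are distorted only if coverage or D differs between the groups compared.
- The obvious remedy, population weights for phase 2 alone, would do harm. Both phases now take 164 per site from communities of about 13,500 and 8,500. Using these totals as a proxy for adults, the weights would move phase 2 to 13,500/22,000 = 61% versus 39%, against an unweighted 50:50 phase 1. If the sites differ by 0.5, that adds (0.614 - 0.5) x 0.5 = 0.057 of new artefact.

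Equal allocation by vaccination status is sensible for the determinants of acceptance, and nothing here argues against it.

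**Conclusion.** The concern holds for the pre/post comparison and for pooled phase 2 levels, for features that differ by vaccination status, when coverage is not 50%. The bias is (0.5 - c) x D. Its size rests on assumed values: with SD 1.5 and D = 0.5, the 5% error rate becomes about 14%, 25% and 40% at 70%, 80% and 90% coverage; at 80% coverage the range is about 10% (D = 0.25) to 69% (D = 1.0). The protocol does not support the wider reading that phase 2 as a whole is compromised. Phase 1 analyses, the vaccinated versus unvaccinated contrasts and the models for actual acceptance are sound on this point, and neither the sampling allocation nor the sample size needs to change. The analysis text does, because a stated objective cannot be met reliably with the tests as named.

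**What to change.** 1. **Reconcile the strata first.** The phase 2 sampling list describes the vaccinated as having had two doses and the unvaccinated as having had one to two doses. The groups overlap. They must be made mutually exclusive and must together cover the adult population before any weight can be formed.

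2. **Weight for pre/post comparisons and pooled phase 2 summaries only.** Within each site-by-gender cell, weight vaccinated respondents by c/0.5 and unvaccinated by (1 - c)/0.5, with c the recorded adult coverage of that cell (1.6 and 0.4 if c = 80%). This keeps the equal site and gender allocation that the phases share. The alternative is to apply population weights for site and gender to both phases as well. Use weighted means or regression with design-based standard errors.

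3. **Leave the rest unweighted:** vaccinated versus unvaccinated contrasts and the logistic models for actual acceptance.

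**Cost.** Analysis wording and survey commands; vaccination status is already to be recorded in the campaign and the frames are in hand. The weighted SE of the phase difference is 1.5 x sqrt(1/328 + (c^2 + (1 - c)^2)/164), with the same coverage in every cell. This is 0.122, 0.127 and 0.135 at 70%, 80% and 90% coverage, against 0.117: increases of about 4%, 9% and 15%. The effective phase 2 sample falls from 328 to 283, 241 and 200. By normal approximation, power for a 0.5 pre/post difference falls from 99.0% to 98.4%, 97.6% and 96.0%, which the sample can bear.

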##### Instrument

The EMIC interview will be exactly the same as in phase 1 except that a special section will enquire about the experience with the vaccination campaign and reasons against getting vaccinated among both unvaccinated and vaccinated respondents.

The interview teams will attend a second week-long workshop where they can refresh their skills and where the new section of the interview will be explained. A second pilot testing phase will take place to adapt the instrument with regard to the new section.

##### Sampling

- Sample: adults (≥ 18 years) from the target areas;

- Sampling frame: vaccination campaign data (vaccinated people), census database after exclusion of vaccinated people (unvaccinated people);

- Sampling method: equally stratified random sample among confirmed vaccinated (two doses of OCV) and unvaccinated (one to two doses) people with gender ratio 1:1;

- Exclusion criteria: belonging to stakeholder level I to III, already interviewed in phase 1, member of household already interviewed;

- Sample size: n = 164 per site, n = 328 per phase

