### Importance of sociocultural and behavioural research on vaccine introduction

Public health interventions to reduce disease burden must take into account the local realities to achieve a sustainable benefit for the affected populations. Solely relying on prevention or treatment measures that proved to be suitable in a given context does not necessarily make it appropriate for other situations.

Vaccination programmes have suffered a reduced coverage (e.g. rumours about tetanus toxoid causing infertility in Tanzania [16]) or were even brought to a halt because of an ignorance of local realities (e.g. Northern Nigerian resistance to polio vaccination [17,18]). Other interventions, especially when implemented in a top-down approach, experienced the same difficulties [19-21].

To ensure the success of vaccination campaigns, a vaccine should not only be efficacious, relatively trouble-free for patients in its administration and preferably also cost-effective, but it is equally important that implementers consider community-held ideas, fears and individual help-seeking behaviour regarding the infectious disease and the vaccine of interest [22,23].

Infrastructure, logistics, politics, and social and cultural features were identified as significant factors which determine vaccine acceptance and thus the success or failure of immunisation programmes in low-income countries [24-26]. The importance of the social and cultural context on vaccine acceptance was assessed in various recent studies for typhoid fever and shigellosis (e.g. in Asian countries [27-31]). It was reasserted that the importance of the social and cultural context on vaccine introduction has to be studied carefully in order to improve vaccination coverage [32].

Research to improve the health of people needs to include gender issues since they play a crucial role in health and health planning [33]. Gender differences are context-specific and thus require that sociocultural and behavioural research be done to complement clinical or epidemiological research. A recent review on the control of tropical diseases concluded that more detailed data about illness experience, meaning and help-seeking behaviour is needed on the gender level to inform the planning and execution of health interventions [34].

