##### EMIC interviews

The interview will enquire about the sociocultural context in terms of illness-related experience, meaning and help-seeking behaviour and about topics related to vaccination. Under experience, different aspects of the illness like physical symptoms and psycho-emotional and social problems and also financial issues that can have an impact on patients will be elicited. Under meaning, respondents will be questioned about their views and opinions on why and how they think one can get the illness with regard to various categories of perceived causes including biological, behaviour-related, social and traditional/magico-religious factors. To find out more about sources of help seeking, respondents will be asked to identify and assess all health care providers, i.e. locally available allopathic and traditional sources, patients suffering from cholera or shigellosis will likely consult. The possible options for self-treatment (at home, not at a health-care provider) will also be elicited.

Variables to be elicited will include:

- Sociodemographic factors

- Categories of diarrhoeal illnesses, name of condition

- Perceived severity of cholera and shigellosis episodes

- Perceived vulnerability of cholera and shigellosis

- Illness experience: operationalised as patterns of distress (PD) related to cholera and shigellosis

- Illness meaning: operationalised as perceived causes (PC) related to cholera and shigellosis

- Illness behaviour: operationalised as help seeking (HS) within and outside the household related to cholera and shigellosis

- Stigma (index) of cholera

- Prior episodes of cholera

- Prevention of cholera

- Experience and perception of vaccinations

- Barriers to vaccination (only phase 2)

- Anticipated vaccination status (only phase 1)

- Willingness-to-pay for OCV

- Actual vaccination status, i.e. vaccinated/unvaccinated, not to be elicited but recorded during vaccination campaign

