Determinants of anticipated and actual OCV acceptance (outcome variables) will be identified in a twofold approach. First, bivariate tests (see above) will be done to see which variables are related with the outcome variables. Then, variables having a suggestive bivariate relationship (p ≤ 0.3) with the outcome variables will be retained as potential explanatory variables for computing stepwise logistic regression models.

Narrative accounts will be used to clarify and substantiate the relationships identified in the above analyses.

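### Actual OCV acceptance in phase 2 is recorded uptake: the planned model cannot by itself separate people who declined from people who were not reached, though the interview collects the reasons

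*Protocol article*

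**What the plan says.** The protocol article fixes the phase 2 outcome in three places.

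- **EMIC interviews (variable list):** "Actual vaccination status, i.e. vaccinated/unvaccinated, not to be elicited but recorded during vaccination campaign".
- **Level IV: phase 2, Sampling:** the strata are an "equally stratified random sample among confirmed vaccinated (two doses of OCV) and unvaccinated (one to two doses) people with gender ratio 1:1". The frame for the second stratum is the "census database after exclusion of vaccinated people (unvaccinated people". No condition is set on being present, offered the vaccine or able to take it.
- **Level IV: quantitative data:** "Determinants of anticipated and actual OCV acceptance (outcome variables) will be identified in a twofold approach", namely a bivariate screen at p ≤ 0.3 followed by stepwise logistic regression.

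The phase 2 Strategy section gives as its third aim "to identify social and cultural determinants of actual OCV acceptance" and as its fourth "to identify barriers to vaccination". The phase 2 Instrument section adds questions on "reasons against getting vaccinated among both unvaccinated and vaccinated respondents". The background section on sociocultural research states: "Infrastructure, logistics, politics, and social and cultural features were identified as significant factors which determine vaccine acceptance".

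**The concern.** A census residual contains people who decided against the vaccine, people who were away or never reached, and people who wanted it but could not take it. The recorded outcome treats them alike. Two things follow if its determinants are read as attitudes.

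- A social or cultural factor that acts only on the decision to decline is diluted, because part of the comparison group resembles the vaccinated on that factor.
- A factor that acts only on access can appear as a determinant of acceptance.

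The comparison with phase 1 is also affected. Anticipated status is collected before the campaign, so it cannot reflect who was actually reached. A difference between the two sets of determinants could come from reach as well as from changed views. The study is meant to advise the Ministry, and unwillingness and poor reach call for different responses.

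**Working it through.** **What the outcome is.** No sentence in the article equates unvaccinated with non-accepting. The variable list makes actual status a two-level record, the Sampling section fills the unvaccinated level from the census residual, and the analysis section models actual acceptance without a further definition. Together these leave recorded uptake as the only available meaning. The reasons are collected, but no section uses them to split the unvaccinated or to define the outcome.

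**The plan's own figure.** Inputs from the sample size section: difference 0.5, SD 1.5, 5% level (taken as two-sided), 80% power.
- n = 2(1.96 + 0.842)² × 1.5² / 0.5² = 141.3, rounded up to 142 per group.
- 142 / 0.864 = 164.35, stated as 164. The figure reproduces and is not in dispute.
- Phase 2 has 328 interviews. Equal strata give 164 vaccinated and 164 unvaccinated.

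**Assumption.** Let f be the share of the unvaccinated who were willing but not reached or unable. The article gives no value, so 20%, 40% and 60% are shown for illustration.

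**Dilution of an attitude factor.** Assume 50% of the vaccinated are exposed and the true odds ratio for declining is 2. Exposure among decliners is then 2/3. Those not reached are assumed to have the same exposure as the vaccinated. Exposure in the mixed group is m = 0.5f + (2/3)(1 − f), and the observed odds ratio is m/(1 − m), because the odds in the vaccinated are 1.

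| f | m | observed odds ratio |
|---|---|---|
| 20% | 0.633 | 1.73 |
| 40% | 0.600 | 1.50 |
| 60% | 0.567 | 1.31 |

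With a true odds ratio of 3 (exposure 0.75 in decliners), the same formula gives 2.33, 1.86 and 1.50.

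**An access factor entering the model.** Assume 30% exposed among the vaccinated, an odds ratio of 3 for being missed and of 1 for declining. Exposure among the missed is 0.5625, and m = 0.5625f + 0.30(1 − f) = 0.353, 0.405 and 0.458. Against the odds of 0.3/0.7 in the vaccinated, the observed odds ratios are 1.27, 1.59 and 1.97. With 164 per group (normal approximation), such a factor passes the p ≤ 0.3 screen about 51%, 83% and 97% of the time. A factor with no association passes 30% of the time.

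**Power for the planned difference of 0.5.** The effective size is 164 × 0.864 = 141.7 per group. In the mixed comparison the difference becomes 0.5(1 − f), and power = Φ(0.5(1 − f) / (1.5√(2/141.7)) − 1.96). For vaccinated v declined, the difference stays 0.5, but the second group shrinks to 141.7(1 − f).

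| f | power, mixed group | declined (of 164) | power, declined only |
|---|---|---|---|
| 0 | 80% | 164 | 80% |
| 20% | 61% | 131 | 75% |
| 40% | 39% | 98 | 68% |
| 60% | 20% | 66 | 56% |

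Under these assumptions the smaller declined group loses less power than the dilution does. This assumes that the reasons classify people correctly.

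**Dose wording.** The vaccinated stratum is two doses and the unvaccinated label is one to two doses. Read as doses received, the labels overlap at two, and the second omits people with no dose, whom the census residual would include. The label may count doses missed, but the article does not say so.

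**The case against.** The strongest reply is that the plan uses acceptance broadly. Its background counts infrastructure and logistics among the determinants of acceptance, alongside social and cultural features. On that meaning, an access factor that emerges from the model is a legitimate finding. This stands. A reader might infer that the planned outcome gives a wrong answer, but the article does not support that: the model answers the uptake question correctly. What remains is that the third objective singles out social and cultural determinants, and a model of uptake does not isolate them.

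A reader might also infer that phase 1 measures pure willingness, so that the two outcomes cannot be compared. The article says only anticipated vaccination status, and the question wording is not shown. Only the weaker statement holds: the two sets of determinants may not be directly comparable.

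A third tempting inference is that the Ministry would be left unaware of access problems. The plan goes against this. Barriers are a separate objective with their own interview section, narratives are to clarify the relationships found, and stakeholder levels I to III also explore barriers after the campaign. Narratives do not, however, change the outcome or recover a determinant lost through dilution.

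Finally, a recorded outcome avoids recall and social desirability, whereas reasons given afterwards do not. This is a good argument against replacing the recorded outcome, but not against a supplementary analysis. The article is also a summary of the full protocol, which may already provide for such an analysis.

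**Conclusion.** The point holds in a limited form. Actual acceptance is recorded uptake, the unvaccinated group mixes people who declined with people not reached or unable, and the collected reasons are not used in the stated model to tell them apart. The planned analysis is valid for uptake and needs no replacement. It cannot alone deliver the social and cultural determinants of the third phase 2 objective.

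The size is not known. The odds ratios and power figures rest on an assumed share, assumed exposure prevalences, and the assumption that people not reached resemble the vaccinated on attitude factors. The upper end of the range should not be read as an expectation: both Shehias are core campaign areas, social mobilisation is planned, and over 90% of the population lives within four kilometres of a primary health care unit. This is an improvement to consider, not a required correction. The overlapping dose labels are a separate textual contradiction that does have to be reconciled.

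**What to change.** 1. Reconcile the dose definitions of the two phase 2 strata, so that each person, including those with no dose or one dose, belongs to exactly one.
2. Keep vaccinated v unvaccinated as the main recorded outcome and label it uptake.
3. Add a supplementary analysis that uses the phase 2 reasons and barriers section to classify unvaccinated respondents as declined, or as willing but not reached or unable. Make one-dose recipients their own category, or assign them by their reason for missing the second dose.
4. Fit a multinomial model, or vaccinated v declined, and report it beside the uptake model. Take care in comparing either with the phase 1 results.
5. Use the second pilot to check that the new interview section separates declining from not being reached.

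The cost is one derived variable and one more model, from data already planned. The declined group will be smaller than 164, and the reasons are self-reported after the event, so the result should be presented as supplementary.
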